## Abstract

**Background:**

In recent years, university counseling and mental health services have reported an increase in the number of clients seeking services and in yearly visits. This trend has been observed at many universities, indicating that behavioral and mental health issues pose significant problems for many college students.

The aim of this study is to assess the acceptability and proof of concept of internet-delivered treatment for depression, anxiety, and stress for university students.

**Methods/design:**

The study is an open feasibility trial of the SilverCloud programs for depression (Space from Depression), anxiety (Space from Anxiety), and stress (Space from Stress). All three are 8-module internet-delivered CBT (iCBT) intervention programs. Participants are assigned a supporter who provides weekly feedback on progress and exercises. Participants will complete the Patient Health Questionnaire-9 (PHQ-9), Generalized Anxiety Disorder-7 (GAD-7), and stress subscale of the Depression, Anxiety, Stress Scale-21 (DASS-21) as the outcome measures for the depression, anxiety, and stress interventions, respectively. Other outcomes include measures of acceptability of, and satisfaction, with the intervention. Data will be collected at baseline, 8 weeks and 3-month follow-up.

**Discussion:**

It is anticipated that the study will inform the researchers and service personnel of the programs’ potential to reduce depression, anxiety, and stress in a student population as well as the protocols to be employed in a future trial. In addition, it will provide insight into students’ engagement with the programs, their user experience, and their satisfaction with the online delivery format.

## Background

Depression, anxiety, and stress are among the primary causes of disease rates worldwide [22] and are the most prevalent mental health problems in the USA [23]. Each is associated with significant economic, personal, intrapersonal, and societal losses including lower quality of life and increased mortality [8, 35, 37].

Depression and anxiety are also the most prevalent mental health problems among the student population [10, 34]. In the 2010 American College Health Survey, 48 % of college and university students reported feeling overwhelming anxiety at least once in the previous year. Thirty-one percent reported feeling so depressed that it was difficult to function at least once in the previous 12 months [2]. More recently, university counseling and mental health services have reported an increase in the number of clients seeking services and in yearly visits [5].

The college years can be a highly stressful time in students’ lives. This is particularly true of the period of transition to college as students are learning to cope with increased academic pressures [27, 48]. Students are at a developmental stage when newfound stressors can promote the onset of mental health difficulties [12, 46, 47]. In addition to academic stress, international students can experience significant sociocultural adjustment demands [19].

Young adults between 17 and 25 years of age are reported to be at greater risk of developing a serious mental illness than individuals in other age groups [51]. Although early diagnosis of mental disorders can be difficult, delayed diagnosis can often lead to treatment resistance and poorer longer-term outcomes [47, 53]. In addition, underachievement or failure at this point in life can cause long-term setbacks to individuals’ self-esteem and future progress [21, 47].

### Treating depression, anxiety, and stress

Depression, anxiety, and stress disorders can each be treated effectively using medications; however, after completing a course of this type of treatment, the chances of relapse are high, and equally successful psychological therapies are available [36]. Of these, cognitive-behavior therapy (CBT) is the most widely researched and CBT is recognized as the leading choice of treatment for depression and anxiety in terms of post-treatment improvements, maintaining progress, and preventing relapse [18, 30]. CBT also is effective for stress management [44]. CBT is comprised of a variety of cognitive and behavioral approaches, each concerned with changing distressing thoughts and beliefs. Treatment is often comprised of self-monitoring and thought recording, behavioral activation, cognitive restructuring, and exposure [11].

### Access to treatment

On a global scale, a significant number of individuals in need of psychological treatment receive no medical diagnosis nor do they seek treatment [1]. The worldwide treatment gap between those needing treatment for depression compared to those receiving treatment has been estimated at 56 %; the gap in treatment for anxiety disorders has been estimated at 46 % [25]. Several factors prevent people from accessing treatment, such as waiting lists, lack of motivation, negative attitudes about treatment, and costs [25, 29]. Among those willing to seek treatment, many encounter a lack of trained professionals or are placed on a waiting list [47]. Although students can often obtain mental health services on campus, many campuses have limited services or have wait lists for services because of the high demand [24]. A survey of US students with mental health problems revealed that common barriers to seeking services, even if they were available, were stigma, lack of time/accessibility, and wait lists [15]. Internet-delivered interventions are one way to address these issues.

### Internet-delivered CBT (iCBT)

Internet-delivered CBT programs are specially designed for the treatment of specific disorders and can be either clinician-guided or self-administered. When such interventions are used in the UK, 6–8 sessions are the recommended length of treatment [31–33]. Many studies provide support for the utility and effectiveness of internet-delivered treatments for depression, anxiety, and stress [4, 10, 38]. Those with the additional feature of human support tend to produce better results [38].

Several studies also have assessed the efficacy of online interventions for depression, stress, and anxiety for college students. Recent reviews of these studies have found evidence for the efficacy of these online interventions [9, 14]. However, most of these studies do not assess the potential for change of the interventions in the context of existing service delivery systems. Rather, many are RCTs assessing efficacy in convenience samples of students (e.g., Psychology majors). The current trial seeks to investigate the acceptability and potential for change of internet-delivered interventions among university students seeking services and the procedures needed to incorporate these interventions into mental health delivery in US universities. Additionally, it hopes to support and extend existing empirical evidence for SilverCloud programs [40–42].

### Objectives of the trial

The aim of this study is to test the acceptability of internet-delivered treatment for depression, anxiety, and stress in university students. The trial will investigate the feasibility of recruiting students (in relation to numbers screened, numbers recruited, and level of adherence) to receive internet-delivered interventions for the treatment of depression, anxiety, and stress and establish the acceptability of the interventions to the students at University of Minnesota.

Acceptability of the intervention to clients will be assessed using data on usage and engagement with the intervention (e.g., percentage of participants completing each module, average number of logins, average time spent per session, and total time spent on the program). These data are acquired through the online SilverCloud system. Satisfaction will be assessed through the use of a post-intervention questionnaire on satisfaction with accessing and using an online delivery format for treatment. At 3 month-follow-up, all 105 participants will be contacted by email and invited to complete a semi-structured interview about their perceptions, attitudes, and experiences of the intervention. The first 25 to respond will be asked to complete the interview. The interview sample will include participants who dropped out of the intervention.

The trial also hopes to establish the potential for change and to establish initial estimates of the effectiveness of these online interventions for students in terms of within-group effect sizes associated with changes in depression, anxiety, and stress from baseline to 8 week and 3 months follow-ups. These data will be used to estimate the sample size for a future trial to ensure that the study is sufficiently powered. A conservative estimate using the 90 % upper confidence limit will be used to inform the sample size calculation of the future RCT.

## Method/design 

### Study design

The study is an open trial of internet-delivered CBT treatment of depression, anxiety, and stress. After completing screening questionnaires, participants will be able to choose one of three online CBT interventions (Space from Depression, Space from Anxiety, and Space from Stress). The study protocol was approved by the University of Minnesota Institutional Review Board (March 18, 2015) (code number: 1503S64741).

### Recruitment procedure

Participants will be recruited through three units at the University of Minnesota-Twin Cities, a public research university located in Minneapolis and St. Paul, Minnesota. The first unit is Student Counseling Services (SCS) which provides free short-term counseling to undergraduate and graduate students. The second is Boynton Mental Health Clinic (BMHC) which also provides short-term psychological services to full-time students at the University of Minnesota. Unlike SCS, BMHC also has psychiatrists on staff and is affiliated with the university health service. Finally, we will recruit participants through the International Student and Scholar Services (ISSS) office which provides counseling to foreign national students on campus.

The SilverCloud programs will be advertised to students through the three participating offices on campus via staff referrals, brochures, flyers, email announcements, and web sites and through the general student mental health web site. Regardless of how they learn about the programs, students can sign up online to get access to the programs. If a student expresses interest, they will be emailed a link to a web site with more information about the programs and the study. Interested students will sign the consent form and complete screening measures online and will be given feedback on their scores. This feedback consists of informing students of their overall score for each measure and whether their score indicates mild, moderate or severe depression, anxiety, or stress. This will allow them to make an informed decision on choosing one of the three programs. They will then be referred to a supporter from within the service where they learned about the study. Participants’ post outcome measures will be gathered 8 weeks after their initial log in or activation of the program and 3 months later (5 months after initial log in).

A second recruitment phase will be conducted at 3-month follow-up. All 105 participants will be contacted by email and invited to complete a semi-structured interview about their perceptions, attitudes, and experiences of the intervention. From those that respond expressing an interest, the first 25 will be selected to complete a semi-structured interview.

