### Sample size

A sample size of 35 participants per group is the standard expectation for feasibility studies [52]. This sample size will allow us to estimate the standard deviation of the symptom outcome measures (for the proposed RCT). We thus aim to recruit 105 participants in total across the three trial arms (see Fig. 1). In addition, a sample of between 10 and 15 people would be suitable to reach saturation through analysis of data collected in semi-structured interviews [16].

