### Trial status

Participant recruitment commenced in October 2015 and is ongoing. Numbers to date are 63.

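### Taking the first 25 responders does not ensure the promised inclusion of dropouts in the interviews, and under-represents them if they reply less readily

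*Protocol article*

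**What the plan says.** The selection rule appears twice. Under Objectives of the trial: "The first 25 to respond will be asked to complete the interview". Under Recruitment procedure: "All 105 participants will be contacted by email and invited to complete a semi-structured interview", and then "From those that respond expressing an interest, the first 25 will be selected to complete a semi-structured interview".

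The Objectives section follows the rule with an unqualified statement about who will be in the sample: "The interview sample will include participants who dropped out of the intervention". It gives no number or share. Neither section mentions reserved places, strata or a reminder to those who do not answer.

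On timing, the Recruitment procedure says "A second recruitment phase will be conducted at 3-month follow-up". In the same section the follow-up assessments are counted from each participant's own first log in. Trial status adds: "Participant recruitment commenced in October 2015 and is ongoing". The article does not say whether the interview invitation is one mailing or is sent participant by participant.

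On the number of interviews, the Sample size section says that "a sample of between 10 and 15 people would be suitable to reach saturation". The figure of 25 has no derivation. Under Measures, the interviews are one of three sources on acceptability, beside platform usage data and the satisfaction questionnaire completed after treatment.

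**The concern.** The article fixes both a selection rule and a result, and nothing connects them. Selection depends on willingness and speed of reply. Students who have stopped using a program may well be less willing to answer an email about it, or slower to do so. That is a plausible inference; the article has no data on it.

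What is at stake is the explanation of non-use. Acceptability is the stated aim. Platform data show that a student stopped but not why. The satisfaction questionnaire asks what was least liked, but dropouts may return it less often. The interviews are the only source of participants' own accounts for which the article says that dropouts will be included. If few or none are interviewed, the themes describe mainly the experience of those who stayed. The Discussion expects the feasibility data to help decide which programs a future trial offers, yet nothing spreads the interviews over the three programs.

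**Working it through.** **Inputs from the protocol.** Pool: 35 per group × 3 = 105, which reproduces the stated total. Interviews: 25, or 25/105 = 24% of the pool. Saturation figure: 10 to 15.

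**Inputs that are assumptions.** The protocol gives neither a dropout rate nor reply rates. Take 40% dropout, so 42 dropouts and 63 completers. A proportional sample would hold 25 × 42/105 = 10 dropouts.

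**Step 1: expected dropouts among 25.** Share of dropouts among responders = 42·r_d / (63·r_c + 42·r_d), multiplied by 25, where r_c and r_d are the reply rates of completers and dropouts.

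| r_c / r_d | Completers replying | Dropouts replying | Dropout share | Of 25 |
|---|---|---|---|---|
| 0.50 / 0.15 | 31.5 | 6.3 | 6.3/37.8 = 16.7% | 4.2 |
| 0.40 / 0.10 | 25.2 | 4.2 | 4.2/29.4 = 14.3% | 3.6 |
| 0.50 / 0.05 | 31.5 | 2.1 | 2.1/33.6 = 6.25% | 1.6 |

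The chance of no dropout in the last row is about (1 − 0.0625)^25 = 0.20. The most favorable corner of these ranges, 0.40 / 0.15, gives 6.3/31.5 = 20%, or 5.0 of 25. With r_c = r_d the share is 40% and the expected number is 10, so there is no shortfall.

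**Step 2: wider range.** Treat the first 25 responders as draws from 105 in which a dropout replies at w times the rate of a completer (Wallenius non-central hypergeometric distribution). Cells show the expected number of dropouts; the chance of none.

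| w | 20% dropout (21) | 30% (32) | 40% (42) | 50% (52) |
|---|---|---|---|---|
| 1 | 5.0; 0.002 | 7.6; <0.001 | 10.0; <0.001 | 12.4; <0.001 |
| 0.5 | 3.0; 0.03 | 4.8; 0.003 | 6.6; <0.001 | 8.7; <0.001 |
| 0.25 | 1.6; 0.17 | 2.8; 0.04 | 4.0; 0.009 | 5.6; 0.001 |
| 0.1 | 0.7; 0.48 | 1.2; 0.27 | 1.9; 0.13 | 2.7; 0.05 |
| 0.05 | 0.4; 0.69 | 0.6; 0.52 | 1.0; 0.36 | 1.5; 0.21 |

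At 40% dropout and w = 0.25 or 0.1 the results are slightly higher than in step 1 (4.0 against 3.6; 1.9 against 1.6), because here the pool of completers shrinks as places fill.

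**Step 3: what selection alone can change.** In the three scenarios of step 1, 29.4 to 37.8 people reply in all, so 25 places take 25/37.8 = 66% to 25/29.4 = 85% of everyone willing. Step 1 has no term for speed of reply: a random choice among the same responders would give the same 1.6 to 4.2. Interviewing every dropout who volunteers would give 2.1 to 6.3. Reaching 10 needs a reply rate of 10/42 = 24% among dropouts, hence a reminder.

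**Step 4: if invitations are rolling.** The overall reply rates in step 1 are 37.8/105 = 36%, 29.4/105 = 28% and 33.6/105 = 32%. The 25 places would then be full after about 25/0.36 = 69 to 25/0.28 = 89 invitations, leaving the last 16 to 36 enrollees without a chance. With a single mailing to all 105 this effect does not arise.

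**The case against.** Dropouts are among the 105 invited, and the Objectives promise no particular number, so one or two would satisfy the statement. A reader might infer that the rule cannot deliver dropouts at all. The documents do not support that: even the least favorable scenario in step 1 leaves about an 80% chance of at least one, and in step 2 the chance of none exceeds one half only where dropouts are 20–30% of the pool and reply at one twentieth of the completers' rate. This part of the objection stands; the rule fails to ensure inclusion, which is a weaker statement.

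A reader might also infer that early enrollees are over-sampled. That needs rolling invitations. Individual follow-up clocks and staggered accrual make these plausible, but contacting all 105 in a second recruitment phase can equally mean one mailing. The point is conditional.

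Third, the low counts in step 1 come from who volunteers, not from who is fastest. This also stands. First-come selection makes matters worse only if dropouts also answer more slowly, and no selection rule can produce volunteers who do not come forward.

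Finally, usage and module-completion data do not depend on interview selection, and the interviews are analyzed thematically and yield no acceptability rate. So the documents do not support a claim that the acceptability evidence as a whole is biased.

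What the objection does not remove is an unqualified statement about the sample, next to a rule that does nothing to bring it about.

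**Conclusion.** The point holds as a gap between the stated composition of the interview sample and the rule that selects it. Its size depends on rates that the protocol does not give. Under 40% dropout and the three reply-rate pairs, about 1.6 to 4.2 of 25 interviewees would be dropouts instead of 10, with up to a 20% chance of none. Under equal reply rates nothing is lost, and under more extreme differences than those pairs the shortfall is larger. The effect is confined to the interview component. Any excess of earlier enrollees is conditional on rolling invitations. This is a modest weakness in design, worth correcting because it touches the study's central aim and needs no additional interviews.

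**What to change.** Keep 25 interviews and replace first-come selection with selection by completion status, taken from the platform's module data.

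- Hold places for non-completers, with a target of up to about 10. Release unfilled places to others only after a reminder has been sent and a set closing date has passed. This should be a target and not a fixed minimum, since under the assumed rates only about 2 to 6 of 42 dropouts would volunteer without a reminder.
- Choose among the remaining volunteers with a spread across the three programs and the recruitment period.
- State whether invitations go out in one mailing or as each participant reaches follow-up.
- Report how many interviewees were non-completers.

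Holding 10 places leaves 15 for others. The saturation figure of 10 to 15 refers to the interview sample as a whole, so it shows that 25 leaves room for both groups but does not set a number for each.

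The cost is a reminder email and later completion of the last interviews. The target may still be missed, in which case the reported count shows it. If first-come selection is kept, soften the Objectives to say that dropouts will be invited and may be included.

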### Sample size

A sample size of 35 participants per group is the standard expectation for feasibility studies [52]. This sample size will allow us to estimate the standard deviation of the symptom outcome measures (for the proposed RCT). We thus aim to recruit 105 participants in total across the three trial arms (see Fig. 1). In addition, a sample of between 10 and 15 people would be suitable to reach saturation through analysis of data collected in semi-structured interviews [16].

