### Eligibility criteria

All registered students at the University of Minnesota will be potentially eligible to participate. Eligibility criteria include being at least 18 years of age and self-reporting mild to severe symptoms of depression (5–27+) on the Patient Health Questionnaire-9 (PHQ-9; [26, 50]), mild to severe symptoms of anxiety (5–21+) on the Generalized Anxiety Disorder (GAD-7; [49]), or mild to severe symptoms of stress (15–34+) on the stress subscale of the Depression, Anxiety and Stress scale-21 (DASS-21; [28]). Students who score below the cutoff score on a given measure may still use the program module related to that measure, although their data will not be included in the analyses. Participants attending face-to-face individual or group counseling will be excluded. This includes all types of psychological therapy such as CBT. At baseline and 3 month assessments, participants will be asked if they have accessed any other form of psychological intervention throughout the time frame of the trial.

Students who score in the “red zone” in terms of risk of self-harm on the screening questions routinely used at SCS (i.e., the Behavioral Health Measure; [6]) will not be referred to the study. Students who score greater than 0 on the PHQ-9 self-harm item in the online screening will be automatically alerted that a counselor will try to reach them. They will be recommended to seek help from BMHC or UCCS. They will be telephoned within 1 working day and contacted by email if they cannot be reached by phone. There is also a “Help” button available on the site which can be accessed at any time and which directs students to a list of counseling resources and health services on campus.

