### Measures

Acceptability data will include information acquired through the online SilverCloud system including data on usage and engagement. In addition, the satisfaction with treatment (SAT) measure will be completed at post-treatment, and finally, data from semi-structured interviews with participants will inform acceptability.

The Patient Health Questionnaire-9 (PHQ-9), the Generalized Anxiety Disorder-7 (GAD-7), the stress subscale of Depression, Anxiety, Stress Scale-21 (DASS-21), and a sociodemographic and history questionnaire will be completed at screening. The following measures, PHQ-9, GAD-7, and stress subscale of DASS-21 will be completed again 8 weeks after their initial log in or activation of the program and 3 months later. All data will be obtained through online self-reported measures.

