### Planned statistical analysis

Acceptability data in terms of usage and engagement will be assessed by analyzing the percentage of participants completing each module, the average number of logins, the average time spent per session, and total time spent on each of the three programs. As mentioned, feasibility will be assessed by analyzing the number of participants recruited at each site and the number of students selecting each of the three programs overall and at each site.

Satisfaction data will be analyzed using the descriptive and interpretative framework described by Elliott and Timulak [13].

Descriptive data will be presented from the semi-structured interviews. The transcriptions will be analyzed thematically using a pre-determined framework derived from the interview schedule and adapted and revised based on participant responses [45].

The outcome data will be treated as preliminary and interpreted with caution. Statistical analysis will be used to describe the characteristics of the sample and to provide initial estimates of parameters needed to inform the design of a future RCT. To assess whether change can be seen in the three programs, within group effect sizes (Cohen’s *d*) assessing change from baseline to 8 weeks and 3 months will be calculated. For Cohen’s *d*, an effect size of 0.2 to 0.3 can be considered a small effect, around 0.5 a medium effect, and 0.8 upwards a large effect [7]. A repeated measure ANOVA will be used to analyze the differences in the symptom outcomes across time points. An estimation of recovery will be made by identifying the number of participants completing each program who demonstrated a reduction of 50 % from pre-treatment PHQ-9, GAD-7, and DASS-21 stress subscale scores [39]. In addition, we will calculate the number of reliably changed and recovered participants using Jacobson and Truax’s [20] criteria.

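### A recruitment total of 105 does not secure 35 analysable participants per programme, because students choose their programme and no quota or allowance for exclusion or attrition is stated

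*Protocol article*

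**What the plan says.** The Sample size section of the protocol article starts from a per-group figure: "A sample size of 35 participants per group is the standard expectation for feasibility studies". It gives the purpose as "This sample size will allow us to estimate the standard deviation of the symptom outcome measures (for the proposed RCT", and then sets the total: "We thus aim to recruit 105 participants in total across the three trial arms". It states no interval width, confidence level or margin for the SD.

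Four other sections bear on whether 35 per group will be reached.

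- **Allocation.** Under Study design, "participants will be able to choose one of three online CBT interventions". Recruitment procedure adds that they choose after seeing their scores and severity bands. The text gives no quota, cap or per-programme stopping rule.
- **The split as a result.** Planned statistical analysis lists among the feasibility outcomes "the number of students selecting each of the three programs overall and at each site".
- **Eligibility and exclusion.** Eligibility criteria joins the three symptom thresholds by an 'or', so one raised score is enough. It adds: "Students who score below the cutoff score on a given measure may still use the program module related to that measure". The same sentence then leaves those students' data out of the analyses.
- **Data available.** Under Measures, every participant completes all three scales at screening, and "PHQ-9, GAD-7, and stress subscale of DASS-21 will be completed again 8 weeks after their initial log in" and once more 3 months later.

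Objectives of the trial says that a 90% upper confidence limit will feed the sample size of the future RCT.

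**The concern.** The move from 35 per group to 105 in total treats the group sizes as fixed by design, whereas elsewhere the protocol treats them as something to be learned. Both cannot hold. Any imbalance in choice takes participants from one programme and gives them to another, so the least chosen programme falls below the figure that justified the sample size. Below-cutoff exclusions and attrition can only lower it further.

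At stake are the per-programme SD and within-group effect size for the least popular programme, which are meant to inform the next trial. A second, smaller matter comes from the same exclusion sentence. It refers to the analyses without limit, so it could be read as also removing consented users from the usage and satisfaction summaries, which serve the study's main aim of acceptability.

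**Working it through.** **Inputs from the protocol article.** 35 per group and 105 in total (Sample size); free choice among three programmes (Study design); 90% upper confidence limit (Objectives of the trial).

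**Inputs assumed.** The preference split, and any rate of exclusion or attrition. The document gives neither.

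**1. The plan's own figure.** 3 × 35 = 105. It reproduces, on condition of an exact three-way tie and no loss.

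**2. Chance that every group reaches 35.** With 105 people and three groups, all three can be at least 35 only if each is exactly 35. Under equal preference the probability is 105! / [(35!)³ × 3¹⁰⁵] = 0.0078, or 0.8%.

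**3. Size of the smallest group.** This comes from simulated draws of multinomial(105; p₁, p₂, p₃), taking the minimum of the three counts. The last column removes each participant independently with an assumed probability of 20%.

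| Split | Mean smallest group | 90% range | Mean smallest with 20% lost |
|---|---|---|---|
| Equal | 30 | 25–34 | 23.6 |
| 40/35/25 (assumed) | 26 | 19–32 | 20.5 |
| 50/30/20 (assumed) | 21 | 14–27 | 16.5 |

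**4. What this does to an SD estimate.** Assume normal data, and take the 90% upper limit as one-sided and applied to the SD. The multiplier on the observed SD is √[(n − 1) / χ²₀.₁₀(n − 1)]. Its square is the inflation of the variance, and so of an RCT sample size proportional to the variance. The relative standard error is 1/√[2(n − 1)].

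| n | Relative SE | Multiplier | Variance inflation |
|---|---|---|---|
| 35 | 12.1% | 1.19 | 1.42 |
| 30 | 13.1% | 1.21 | 1.47 |
| 26 | 14.1% | 1.23 | 1.52 |
| 21 | 15.8% | 1.27 | 1.61 |

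For n = 35: √(34 / 23.95) = 1.191, and 1.191² = 1.42. For n = 21: √(20 / 12.44) = 1.268, and 1.268² = 1.61.

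Relative to n = 35, the RCT would grow by 1.47/1.42, about 3%, at n = 30, and by 1.61/1.42, about 13%, at n = 21.

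**5. What pooling could offer.** All participants complete all three scales, so the SD of each scale need not come from one programme's choosers alone. The ceiling is all 105: √(104 / 86.00) = 1.10, variance inflation 1.21. The number above each cutoff is not known, so the actual gain lies somewhere short of this.

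**6. A dependency.** The number excluded from the stress programme turns on its threshold. Eligibility criteria says "or mild to severe symptoms of stress (15–34+) on the stress subscale", while Symptom outcome measures gives the summed stress score a range of 0 to 21. The two sections must be reconciled before the size of that exclusion can be judged.

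**The case against.** The strongest reply is that little is lost. The protocol says only that the SD can be estimated, and it can be at 20 to 30 participants. The 0.8% is the probability of an exact tie and does not measure practical harm: under equal preference the multiplier moves only from 1.19 to 1.21. The outcome results are also declared preliminary. All of this stands, and it limits the point to a group size that is not secured, with a small to moderate effect on precision.

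Four stronger readings are tempting, and the document does not support them.

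- *A reader might infer that a promised SD precision is missed.* None is promised in Sample size. Objectives of the trial names neither the parameter nor the sidedness of its 90% limit, and mentions it after within-group effect sizes. The multipliers above rest on one interpretation of it.
- *A reader might infer that one programme is bound to fall well short of 35.* The uneven splits are assumptions, and under equal preference the expected shortfall is about five.
- *A reader might infer that some of the 105 are certain to be unanalysable.* The 'or' in the eligibility rule allows it, but the text does not say whether below-cutoff users count towards the 105. Feedback on scores before the choice should also limit mismatches. The rate is unknown.
- *A reader might infer that these users are removed from the feasibility results.* The wording is ambiguous. It stands in an eligibility paragraph and may mean outcome analyses only, and the Acceptability section plans recruitment-flow counts without mention of a cutoff.

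Fig. 1 is not available here and may show numbers per programme. That would not answer the point, because a printed number does not enforce a split when students choose freely.

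**Conclusion.** The point holds in limited form: 105 is a total and does not secure 35 analysable participants in each programme. That follows from the protocol's own text on choice, on the split as an outcome and on eligibility by any one measure, and from the absence of any stated quota or allowance for loss. Only the equal-preference result (smallest group about 30) is free of an assumed uneven split, and it already falls short of 35 before exclusions or attrition. The figures of 26 and 21 depend on assumed splits, and the multipliers depend on normality and on reading the 90% limit as one-sided for the SD. On that reading, the RCT inflation factor rises from 1.42 to between 1.47 and 1.61. This is worth correcting, but it does not undermine the study, and it is no reason to recruit more people.

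**What to change.** 1. In Sample size, keep 105 but describe it as a total that does not guarantee 35 per programme. State the range expected for the smallest programme and the SD precision at that size, and say whether below-cutoff users count towards the 105.
2. Estimate each measure's SD from all participants above that measure's cutoff, adjusting for programme, and report the per-programme SDs alongside.
3. State that the below-cutoff exclusion applies to the symptom-change analyses. Recruitment, usage and satisfaction summaries then keep all consented users, with below-cutoff users shown separately.

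The cost is wording plus one further analysis of data already being collected, with no extra recruitment. The downside is that pooling assumes similar spread among students who chose different programmes, and the small per-programme groups can check this only roughly. Trial status reports 63 recruited with recruitment continuing, so when the article was written the change could still be made before the analysis.
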